#### Accelerometer

2.4.4

Participants will wear an accelerometer on their non‐dominant arm for 8 days to capture habitual activities, sleep duration and quality, overall physical activity volume and intensity profile, along with time spent sedentary, in light‐intensity physical activity, and in moderate‐to‐vigorous physical activities.

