#### Continuous glucose monitors (CGMs)

2.4.5

All participants will be offered CGM devices (Freestyle Libre 2) to ensure trial results are obtained in the context of optimised usual care. CGMs will be optional; we will perform exploratory analyses of sensor glucose levels. Data will be downloaded remotely via LibreLink.

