#### Blinding

2.4.8

Given the design of the intervention, the study team and participants will not be blinded to the intervention. The study statistician is masked, but no code‐break or emergency unblinding will be required. To reduce bias, the primary and most of the secondary outcomes will be collected from the participants' medical records rather than specifically collected for the study. The patient‐reported secondary outcomes will be collected using validated questionnaires. As such, there are no outcome assessors involved in the study.

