#### Public and patient involvement and engagement (PPIE)

2.5.2

PPIE members informed the design of the MiFoot intervention and RCT, including reviewing patient‐facing documentation, lay summaries and dissemination strategies. PPIE members will be proactively involved throughout the trial to support participant recruitment, data collection, results interpretation and dissemination. A PPIE member also sits on the Trial Steering Committee.

The MiFoot programme is a complex, multifactorial, evidence‐based, theory‐driven, person‐centred intervention designed to improve cardiovascular health and fitness and comprises three components:
An individualised 1:1 appointment with an HCP that focuses on medical management and intensive multifactorial CVD risk‐factor control like glycated haemoglobin (HbA1c), blood pressure, body mass index (BMI), anxiety, depression and lipids. An evidence‐based, pictorial health profile is used to plot baseline measurements and is used to help participants understand their health measurements, facilitate discussions and a formulate an agreed treatment plan. Participants' medical history will be reviewed, contraindications to exercise screened for and advice regarding weight‐bearing status for those with active foot ulcer disease as well as the intensity of physical activity (light or moderate) will be carried out during this appointment. An ECG will also be carried out. This appointment will also help address clinical inertia.Group‐based disease self management education and physical activity sessions, comprising education regarding disease knowledge, risk‐factor control, diet and weight management, physical activity, emotional management and goal setting. Sessions will include opportunities for physical activity instruction, participation and supervision. Participants' heart rate and rated perceived exertion will be monitored during the physical activity sessions to ensure an appropriate response to activity as well as that the intensity of activity is not exceeded. These sessions are delivered by two trained facilitators, at least one of whom is an HCP.A bespoke DFUD‐related digital programme, based on the pre‐existing MyDesmond platform for the management of T2D, to supplement the group‐based sessions, comprises relevant learning sessions, physical activity guidance, health trackers, ask‐the‐expert functionality and forums for peer support.

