### Follow‐up assessments

3.1

Participants will be followed up for 24 months using the same measures as the baseline visit through questionnaires, accelerometers, routine health data and health outcomes (Tables 1 and 2). There will be no on‐site visits for the 12‐ and 24‐month assessments.

**TABLE 2 dme70028-tbl-0002:** Schedule of procedures.

Procedures	Visits			
	Pre‐screening	Baseline visit, Month 0	Remote, 12‐month follow‐up	Remote, 24‐month follow‐up
Invitation and EOI	XX			
Telephone screening	XX			
Informed consent		XX		
Face to face eligibility screening		XX		
Demographics		XX		
Baseline Research Data Extraction		XX		
SINBAD Score		XX		
Consent		XX		
Inform GP of study participation		XX		
Randomisation		XX		
Anthropometric		XX	XX	XX
Patient‐reported outcomes Questionnaires		XX	XX (±4 weeks)	XX (±4 weeks)
Accelerometer		XX (±4 weeks)	XX (±4 weeks)	XX (±4 weeks)
CGM provision		XX^a^		
ECG		X		
Health outcomes data collection		XX	XX	XX
Biomedical markers		XX	XX	XX
Physical activity screening		X		
Adverse event assessments Safety measures		X	X	X
Process evaluation observations		X		
Process evaluation feedback surveys		X^b^		
Process evaluation questionnaires			X	
Process evaluation interviews				After 24th month

*Note*: X: Intervention arm only; XX: All study participants.

Abbreviations: ECG, electrocardiogram; EOI, expression of interest; GP, general practitioner; SINBAD, ulcer site, ischemia, neuropathy, bacterial infection, area and depth.

^a^
All participants will be offered CGM devices at their baseline appointment; though if they decline at this stage, they can change their mind throughout the trial.

^b^
After each one‐to‐one and group sessions and 4 weeks after the digital programme, collected up to month 9 of the intervention delivery.

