## Statistical analysis

7

A full statistical plan will be finalised prior to database lock before any unblinded data has been seen by the statistician. The primary analysis will compare the primary outcome (extended MACE at 24 months) between treatment groups using a Cox proportional hazards regression model, assuming assumptions are met. The model will be fitted with time to extended MACE as the outcome and treatment group as the main explanatory variable. The stratification factors (site, age, sex) will be adjusted for, and participants lost to follow‐up will be censored at the last date at which they were known to be event‐free. If any baseline imbalances become evident, these will be investigated using secondary exploratory analyses.

For the event outcomes (renal end points, extended MACE components and all‐cause mortality, amputation), the analysis approach will be a Cox proportional hazards model adjusted for the stratification factors in line with the primary analysis. The questionnaire summary measures, biomedical markers and anthropometric measures will be compared between treatment groups using linear mixed regression models adjusted for time (baseline, 12 and 24 months) and the stratification factors. Missing data for non‐event outcomes will be imputed using multiple imputation where data can be assumed to be missing at random. A sensitivity analysis will be carried out removing any variables with >10% missing data.

Summary measures (number of events or mean change from baseline) by treatment group, effect size, 95% confidence interval and two‐sided *p*‐value will be presented for each of the primary and secondary analyses. Statistical significance will be assessed at the 5% level.

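### The schedule lets the baseline accelerometer recording be made after allocation, by unblinded participants, so change from baseline in activity and sleep may subtract an early effect

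*Protocol article*

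**What the plan says.** Section 2.4.4 has the accelerometer worn on the non-dominant "arm for 8 days to capture habitual activities, sleep duration and quality, overall physical activity volume" and intensity. Table 1 lists these measures as secondary outcomes at baseline, 12 and 24 months.

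Table 2 has one baseline column, headed "Baseline visit, Month 0". It contains informed consent, face-to-face eligibility screening, randomisation and the baseline accelerometer, whose cell carries a window of ±4 weeks. The baseline questionnaire cell in that column has no window.

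The key to Table 2 reads "X: Intervention arm only; XX: All study participants". Under it, the ECG and the physical activity screening in the baseline column are for the intervention arm only. The description of the 1:1 intervention appointment (section 2.5) says "An ECG will also be carried out".

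Section 2.4.8 states that "the study team and participants will not be blinded to the intervention".

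On glucose sensors, footnote a of Table 2 says "All participants will be offered CGM devices at their baseline appointment", and those who decline may take one up later. Section 2.4.5 says "CGMs will be optional; we will perform exploratory analyses of sensor glucose levels". Table 1 nevertheless lists CGM metrics at baseline.

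Section 7 compares questionnaire, biomedical and anthropometric measures with "linear mixed regression models adjusted for time (baseline, 12 and 24 months) and the stratification factors". It reports mean change from baseline as the summary measure for non-event outcomes across the primary and secondary analyses.

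**The concern.** A baseline value is useful because allocation cannot have influenced it. Here the recording takes more than a week, and its window is centred on the visit at which Table 2 also schedules randomisation. Nothing in the article makes randomisation, disclosure of the arm or the first intervention contact wait until wear is complete.

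A participant who has just learned that they will receive an activity programme may move more that week, and one allocated to usual care may not. Any such difference is specific to one arm. It is then treated as a pre-existing difference and subtracted from the later comparison. Physical activity is a direct behavioural target of the intervention, so this is the secondary outcome for which an uncontaminated baseline matters most.

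**Working it through.** **No figure in the plan to reproduce.** The article states no sample size or effect size for accelerometer or CGM outcomes. The stated 372, and 392 after 5% dropout (372 / 0.95 = 391.6), concern extended MACE and do not depend on this point.

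**Step 1: the timeline as scheduled.**

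| Element | Place | Consequence |
|---|---|---|
| First consent | Table 2, Month 0 | No trial recording before this visit |
| Randomisation | Table 2, Month 0 | Allocation may be known from this visit |
| Wear of 8 days | Section 2.4.4 | Cannot be completed within the visit |
| Window of ±4 weeks | Table 2, accelerometer row | Minus side falls before consent; plus side runs to 4 weeks after the visit |
| ECG and activity screening, one arm only | Table 2, Month 0; section 2.5 | Intervention contact may fall within the same period |
| No blinding of participants | Section 2.4.8 | Participants know their arm |

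If consent and randomisation fall on day 0, the earliest complete recording covers days 0 to 8, and the window allows later ones. All of it then follows allocation.

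**Step 2: effect on the estimates.** Let τ be the true between-arm difference at 12 or 24 months, f the fraction of τ already present in the baseline recording, and rho the correlation between baseline and follow-up, with equal standard deviations. For an effect that is sustained:

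- Change from baseline estimates τ − fτ = τ(1 − f).
- A baseline-adjusted comparison estimates τ − rho·fτ = τ(1 − rho·f).

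The article gives neither f nor rho. The values below are assumptions that show the range.

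| f | Change score keeps | Adjusted, rho 0.3 | rho 0.5 | rho 0.7 |
|---|---|---|---|---|
| 0 | 100% | 100% | 100% | 100% |
| 0.10 | 90% | 97% | 95% | 93% |
| 0.25 | 75% | 92.5% | 87.5% | 82.5% |
| 0.50 | 50% | 85% | 75% | 65% |

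**Step 3: where it enters the analysis.** Table 1 files the accelerometer measures under patient-reported outcomes. The mixed-model sentence in section 7 does not name them, so their place in that model is likely but not stated. The change-from-baseline summary covers the secondary analyses generally, and there the loss is f.

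**Step 4: CGM.** The trial sensor is first supplied at the baseline appointment or later. A participant who takes one up later in the trial cannot have a pre-allocation value from it.

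**The case against.** The strongest reply is that the order is inferred. The baseline column of Table 2 is not a single sitting: it also holds feedback surveys that footnote b extends to month 9, so sharing a column does not prove same-day consent and randomisation. Section order (accelerometer before randomisation) and row order in Table 2 (randomisation above accelerometer) point opposite ways, and neither is a timing rule. Figure 1, which may show the sequence, is not available here, and the full protocol may settle it.

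This stands to the extent that one cannot say baseline wear *does* follow allocation in every participant. It does not remove the point. The ±4-week window is a stated rule, its minus side is unusable when consent is first taken at Month 0, and nothing in the article closes the plus side.

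A reader might also infer that a third to a half of the activity effect is lost. The documents do not support that. No start date is given for the 1:1 appointment or group sessions, screening must precede activity, and every component is optional, so f in the first days could be close to zero.

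Nor do they support extending the point to the baseline questionnaires, whose cell has no window.

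**Conclusion.** The point holds as a statement about what the schedule permits: baseline activity and sleep may be recorded up to 4 weeks after the visit that contains randomisation, by unblinded participants, with intervention contact possible in that period. It would fall away if randomisation or disclosure in practice waits for completed wear, but the article does not say so.

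The size is unknown. The change-score loss equals f: nil if f is near zero, 10–50% under an assumed f of 0.10 to 0.50. A baseline-adjusted estimate loses less; over that range of f and rho of 0.3 to 0.7 the loss is 3–35%. These figures assume a sustained effect and equal variances.

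The scope is narrow. A reader might infer a threat to the main result, but extended MACE comes from routine records and does not use this baseline. The affected outcomes are the secondary accelerometer measures and, with less consequence, the optional and exploratory CGM metrics. The change is still worth making because the bias is specific to one arm, affects a behaviour the intervention targets, and is cheap to prevent.

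**What to change.** - **Schedule.** Replace the ±4-week baseline accelerometer window with a requirement that the 8-day wear is completed after consent and before allocation is disclosed, or at least before first intervention contact. The 24-hour online randomisation system allows allocation away from the visit. If sites already work this way, one sentence saying so is enough.
- **Analysis.** Where wear followed allocation, compare 12- and 24-month values between arms without using that recording as a baseline.
- **CGM.** Do not label sensor data collected after allocation as baseline.
- **Questionnaires.** No change to their baseline timing is supported.

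**Cost.** The delay is roughly 8–10 days between visit and randomisation, with a slight risk of losing participants before randomisation. If the 3-month feasibility count is taken at randomisation (the article does not say) and accrual is even at 98 over about 90 days, the delay moves 98 / 90 × 8 to 98 / 90 × 10, or about 9 to 11 participants, past that count. That leaves 87 to 89 against the green threshold of 78.

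Omitting the baseline value costs precision. Relative to a baseline-adjusted analysis, the variance of a follow-up comparison is multiplied by 1 / (1 − rho²): 1 / 0.91 = 1.10, 1 / 0.75 = 1.33 and 1 / 0.51 = 1.96 for assumed rho of 0.3, 0.5 and 0.7. Completing wear before disclosure is therefore better than relying on the analysis remedy.

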#### Continuous glucose monitors (CGMs)

2.4.5

All participants will be offered CGM devices (Freestyle Libre 2) to ensure trial results are obtained in the context of optimised usual care. CGMs will be optional; we will perform exploratory analyses of sensor glucose levels. Data will be downloaded remotely via LibreLink.

#### Questionnaires

2.4.6

Participants will complete the following questionnaires at baseline, 12 and 24 months (Table 1):
EuroQol 5‐Dimension 5‐Level (EQ‐5D‐5L): Measures health‐related quality of life (QoL) specifically in chronic health conditions.Hospital Anxiety and Depression Scale (HADS): Measures the severity of symptoms of anxiety and depression.ModRUM: Includes questions on healthcare resource use covering emergency care, outpatient care, GP visits (including home‐visit or remotely accessed) and NHS HCP visits.Diabetic Foot Ulcer Scale–Short Form (DFS‐SF): Assesses the impact of foot ulcers and their treatment on the QoL of people with diabetes.Diabetes Self Management Efficacy Scale (DMSES‐15): Assesses respondents' confidence levels in their blood sugar, diet and level of exercise management.Problem Areas in Diabetes Questionnaire (PAID‐20): Measures diabetes stress.Morisky Medication Adherence Scale (MMAs‐8): Measures medication‐taking behaviour.Diet (short‐form food frequency questionnaire): Assesses dietary habits.

#### Randomisation

2.4.7

Participants will be randomly allocated 1:1 to the control or intervention arm using an online 24‐h system provided by the Derby Clinical Trials Support Unit (DCTSU). Block randomisation will be stratified by site, sex (men; women) and age (<50; ≥50 years).

#### Blinding

2.4.8

Given the design of the intervention, the study team and participants will not be blinded to the intervention. The study statistician is masked, but no code‐break or emergency unblinding will be required. To reduce bias, the primary and most of the secondary outcomes will be collected from the participants' medical records rather than specifically collected for the study. The patient‐reported secondary outcomes will be collected using validated questionnaires. As such, there are no outcome assessors involved in the study.

### Intervention

2.5

#### The MiFoot programme

2.5.1

#### Public and patient involvement and engagement (PPIE)

2.5.2

PPIE members informed the design of the MiFoot intervention and RCT, including reviewing patient‐facing documentation, lay summaries and dissemination strategies. PPIE members will be proactively involved throughout the trial to support participant recruitment, data collection, results interpretation and dissemination. A PPIE member also sits on the Trial Steering Committee.

The MiFoot programme is a complex, multifactorial, evidence‐based, theory‐driven, person‐centred intervention designed to improve cardiovascular health and fitness and comprises three components:
An individualised 1:1 appointment with an HCP that focuses on medical management and intensive multifactorial CVD risk‐factor control like glycated haemoglobin (HbA1c), blood pressure, body mass index (BMI), anxiety, depression and lipids. An evidence‐based, pictorial health profile is used to plot baseline measurements and is used to help participants understand their health measurements, facilitate discussions and a formulate an agreed treatment plan. Participants' medical history will be reviewed, contraindications to exercise screened for and advice regarding weight‐bearing status for those with active foot ulcer disease as well as the intensity of physical activity (light or moderate) will be carried out during this appointment. An ECG will also be carried out. This appointment will also help address clinical inertia.Group‐based disease self management education and physical activity sessions, comprising education regarding disease knowledge, risk‐factor control, diet and weight management, physical activity, emotional management and goal setting. Sessions will include opportunities for physical activity instruction, participation and supervision. Participants' heart rate and rated perceived exertion will be monitored during the physical activity sessions to ensure an appropriate response to activity as well as that the intensity of activity is not exceeded. These sessions are delivered by two trained facilitators, at least one of whom is an HCP.A bespoke DFUD‐related digital programme, based on the pre‐existing MyDesmond platform for the management of T2D, to supplement the group‐based sessions, comprises relevant learning sessions, physical activity guidance, health trackers, ask‐the‐expert functionality and forums for peer support.

The intervention components are displayed in Figure 2. The intervention development process will be further detailed in a future publication.

**FIGURE 2 dme70028-fig-0002:**
[figure not shown]
Components of the MiFoot Intervention.

Prior to participation in the physical activity component of the intervention, participants will undergo precautionary screening to ensure safety. This will include an electrocardiogram (ECG) to identify any potential undiagnosed cardiac problems, assessment of any active ulcers and completion of a specifically designed assessment form to safely determine participants' readiness and ability for physical activity.

## Outcomes

3

The primary outcome is the incidence of extended Major Adverse Cardiovascular Events (MACE) at 24 months, identified using routine healthcare data. The extended MACE definition for MiFoot is context‐specific and is defined as myocardial infarction, stroke, cardiovascular death, peripheral arterial bypass, coronary artery bypass, coronary angioplasty or peripheral artery angioplasty.^16^ The secondary outcomes are health, patient‐reported, biomedical and anthropometric outcomes, described in Table 1.

### Follow‐up assessments

3.1

Participants will be followed up for 24 months using the same measures as the baseline visit through questionnaires, accelerometers, routine health data and health outcomes (Tables 1 and 2). There will be no on‐site visits for the 12‐ and 24‐month assessments.

**TABLE 2 dme70028-tbl-0002:** Schedule of procedures.

Procedures	Visits			
	Pre‐screening	Baseline visit, Month 0	Remote, 12‐month follow‐up	Remote, 24‐month follow‐up
Invitation and EOI	XX			
Telephone screening	XX			
Informed consent		XX		
Face to face eligibility screening		XX		
Demographics		XX		
Baseline Research Data Extraction		XX		
SINBAD Score		XX		
Consent		XX		
Inform GP of study participation		XX		
Randomisation		XX		
Anthropometric		XX	XX	XX
Patient‐reported outcomes Questionnaires		XX	XX (±4 weeks)	XX (±4 weeks)
Accelerometer		XX (±4 weeks)	XX (±4 weeks)	XX (±4 weeks)
CGM provision		XX^a^		
ECG		X		
Health outcomes data collection		XX	XX	XX
Biomedical markers		XX	XX	XX
Physical activity screening		X		
Adverse event assessments Safety measures		X	X	X
Process evaluation observations		X		
Process evaluation feedback surveys		X^b^		
Process evaluation questionnaires			X	
Process evaluation interviews				After 24th month

*Note*: X: Intervention arm only; XX: All study participants.

Abbreviations: ECG, electrocardiogram; EOI, expression of interest; GP, general practitioner; SINBAD, ulcer site, ischemia, neuropathy, bacterial infection, area and depth.

^a^
All participants will be offered CGM devices at their baseline appointment; though if they decline at this stage, they can change their mind throughout the trial.

^b^
After each one‐to‐one and group sessions and 4 weeks after the digital programme, collected up to month 9 of the intervention delivery.

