#### Baseline research data extraction

2.4.3

Routine health data, medical history, all current diagnoses and dates, procedures/surgeries and medications, will be extracted from participants' medical records. Routine biomarker results, as listed in Table 1, that are within 6 months, will be extracted or requested through the GP.

**TABLE 1 dme70028-tbl-0001:** Secondary outcomes, measures and time of measurement during the study.

Secondary outcomes	Measures	Visits		
		Baseline visit, Month 0	Remote, 12‐month follow‐up	Remote, 24‐month follow‐up
Health outcomes	Composite renal end points: End‐stage kidney disease (defined as dialysis, transplantation, or a sustained (>3 months) estimated Glomerular Filtration Rate [eGFR] of <15 mL/min/1.73 m^2^) Doubling of the serum creatinine level Or death from renal causes 3‐Point MACE (non‐fatal myocardial infarction, non‐fatal stroke and cardiovascular death) and components of the extended MACE All‐cause mortality Lower limb major amputation Self reported re‐ulceration		X	X
Patient‐reported outcomes	Using Questionnaires: Distress using Problem Area in Diabetes‐20 (PAID‐20) Self‐efficacy using Diabetes Management Self‐Efficacy Scale‐15 (DMSES‐15) Quality of Life using Diabetes Foot Ulcer Disease (Diabetes Foot Scale‐Short Form [DFS‐SF], generic EuroQoL‐5Dimension‐5Levels [EQ‐5D‐5L]) Depression and anxiety using Hospital Anxiety and Depression Scale (HADS) Health resource use, such as primary care visits, emergency department visits, hospitalisations and medication use using Modular Resource‐Use Measure (ModRUM) Medication adherence using the Morisky Medication Adherence Scale (MMAS‐8) Diet using the Short Form Food Frequency Questionnaire Sleep duration/quality and physical activity volume/intensity measured objectively using wrist worn accelerometers	X	X	X
Biomedical markers	Blood pressure (systolic, diastolic and heart rate) (mmHg, BPM) Low‐density lipoprotein‐cholesterol (LDL‐C) (mmol/L) High‐density lipoprotein‐cholesterol (HDL‐C) (mmol/L) Total cholesterol (TC) (mmol/L) Triglycerides (TG) (mmol/L) Glycated haemoglobin (HbA1c) (% and mmol/mol) Estimated Glomerular Filtration Rate (eGFR) (mL/min/1.73 m2) Urine albumin: creatinine ratio (uACR).	X	X	X
Anthropometric	Weight Body mass index (BMI)	X	X	X

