## DISCUSSION

8

Considering the prevalence of DFUD, the mortality due to CVD in people with T2D and DFUD, the resulting financial burden on the NHS,^1^, ^22^ and the limited evidence on the topic, this study is important to investigate CVD‐risk modification in this extremely at‐risk population. Notwithstanding that CVD is the leading cause of death in people with DFUD,^9^ ulcer management and/or prevention, but not CVD risks,^12^ continue to be the main focus of research and routine care^10^ in people with DFUD. While extant literature supports physical activity and exercise for blood glucose management in people living with diabetes,^23^ patients with DFUD are often told to limit weight‐bearing activity due to concerns of increased risk of foot ulcers and amputation.^24^

A Delphi study generated recommendations for physical activity and exercise in patients with diabetes at risk of ulceration.^25^ Moreover, the International Working Group on the Diabetic Foot (IWGDF) guidelines recommend that an ideal intervention for the DFUD population will consist of adequate foot ulcer offloading and increased activity levels that promote both effective ulcer healing and provide an improvement in cardiovascular health and quality of life,^26^ while ensuring participant safety. The MiFoot RCT aligns with both and has been developed to consider participants' clinical and mental health, and the SINBAD score if ulceration is active, to determine the physical activity intensity and weight bearing capacity of participants, thus providing a safe pathway for participants to exercise.

Diabetes self management education (SME) programmes are efficacious and cost‐effective in promoting and facilitating diabetes self management knowledge and skills acquisition. The 1:1 component creates an avenue for this cohort to have extra care tailored to their current health, while the social interaction during the group session component promises to address diabetes distress.^27^

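### Table 2 schedules adverse event assessment in the intervention arm only, so adverse events that are not study outcomes cannot be compared between arms

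*Protocol article*

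**What the plan says.** Table 2 in section 3.1 (Follow-up assessments) lists "Adverse event assessments Safety measures" as one row, marked with a single X at the baseline, 12-month and 24-month columns. The note under the table defines the marks: "X: Intervention arm only; XX: All study participants". Nothing else in the article describes adverse event collection in the control arm.

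The same table marks "Health outcomes data collection" with XX at all three time points, so that row covers everyone. Table 1 shows what it contains: a composite renal end point, 3-point MACE and the components of extended MACE, all-cause mortality, "Lower limb major amputation" and self-reported re-ulceration. For renal end points, extended MACE components, all-cause mortality and amputation, section 7 (Statistical analysis) states that "the analysis approach will be a Cox proportional hazards model adjusted for the stratification factors in line with the primary analysis".

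The Discussion (section 8) notes that patients with foot ulcer disease are often advised to limit weight-bearing activity "due to concerns of increased risk of foot ulcers and amputation". It describes the use of health status and, where an ulcer is active, the SINBAD score to set activity intensity and weight bearing, "thus providing a safe pathway for participants to exercise".

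**The concern.** The programme combines physical activity with intensive control of risk factors, including HbA1c and blood pressure, in people who may have an active foot ulcer. Falls, musculoskeletal injury, symptomatic hypotension, hypoglycaemic episodes and deterioration of an ulcer are plausible unwanted effects. They could also occur in this population without the programme. A count from one arm alone cannot separate what the programme adds from what would have happened anyway.

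If Table 2 is followed as printed, the report will hold an adverse event listing for one arm and nothing to set beside it. A high count could be read as harm, or a low count as reassurance, and neither reading would be supported. Information not gathered in the same way in both arms during follow-up is also hard to recover later.

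**Working it through.** **1. Is the single X a deliberate mark?** The table uses its two marks distinctly. Questionnaires, accelerometry, anthropometry, biomedical markers and health outcomes carry XX. ECG, physical activity screening and the process evaluation rows carry X. By the table's own key, the adverse event row belongs to the intervention-only group.

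**2. Could the row mean only monitoring of programme sessions?** The timing argues against it. The marks stand at the general follow-up points, including the remote 12- and 24-month contacts. Table 2 footnote b ties the feedback surveys to each session and ends their collection at month 9 of delivery. The adverse event row has no such note.

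**3. How many participants are affected?** Section 4 gives 372 participants before dropout and 392 after a 5% allowance: 372/0.95 = 391.6, rounded up to 392. With 1:1 allocation (section 2.4.7), 392/2 = 196 per arm. Adverse event assessment therefore covers about 196 intervention participants and 0 controls.

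**4. Which harms have a measure in both arms?**

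| Possible harm | Measure scheduled in both arms | Limit |
|---|---|---|
| Death, cardiovascular events, renal events | Health outcomes (Table 1), Cox models (section 7) | None material to this point |
| Amputation | Major amputation, Cox model | Major only |
| New ulcer | Re-ulceration | Self-reported by unblinded participants; not in section 7's list of event outcomes |
| Worsening of an existing ulcer | No clinical measure; DFS-SF records impact on quality of life | SINBAD is scheduled at baseline only |
| Hypoglycaemia | CGM time below range | CGM is optional and its analysis exploratory; not a count of symptomatic episodes |
| Hypotension | Blood pressure | A proxy, not a count of symptomatic events |
| Emergency visits, hospitalisation | ModRUM | Service use, not an adverse event assessment |
| Falls, musculoskeletal injury | None named | No control-arm rate |

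**5. What would collection in both arms give?** The article states no adverse event risks, so control risks of 10%, 20% and 30% are assumed here. With n = 196 per arm and equal risk p, the 95% half-width for a risk difference is 1.96 × √(2p(1 − p)/n).

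- p = 10%: 1.96 × √(0.18/196) = 5.9 percentage points
- p = 20%: 1.96 × √(0.32/196) = 7.9 percentage points
- p = 30%: 1.96 × √(0.42/196) = 9.1 percentage points

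Using the normal approximation for two proportions, two-sided 5% and 80% power, the increases detectable with 196 per arm are roughly 10% to 20%, 20% to 32.5%, and 30% to 44%. Collection in both arms would thus show large excesses in common events and give usable intervals. With one arm only, the control term is missing and no difference can be formed at any risk.

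**The case against.** The strongest reply is that the important harms are already covered. That largely stands. Death, MACE components, renal events and major amputation are collected in everyone and compared by Cox model. Re-ulceration, service use, blood pressure, eGFR and mood and distress scores are also scheduled in both arms. A reader might infer from Table 2 that the trial cannot say whether the programme causes harm. The document does not support that. Ulcers and amputation, the harms the Discussion itself names, are both collected in both arms, although re-ulceration is the weaker measure.

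Three further inferences are tempting and also go too far.

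- **Bias in the primary outcome.** One might suppose that extra enquiry in one arm would bring more cardiovascular events to light. Section 2.4.8 says that, for the primary and most secondary measures, "outcomes will be collected from the participants' medical records rather than specifically collected for the study", and section 3 takes extended MACE from routine healthcare data. Nothing shown makes adverse event enquiry a source of MACE events.
- **A disabled monitoring committee.** Section 6.1 describes only the committee's recommendation on recruitment. The article does not say which safety data it reviews.
- **An unsupported safety claim.** The Discussion's remark about a safe pathway describes screening and tailoring of exercise. It does not assert comparative safety.

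A last reply is that this is a journal article, and that the full protocol may specify adverse event reporting in both arms or use this row for programme-related monitoring. That is possible, and it is why the fix starts with confirmation. It does not remove the point, because the article is not silent: it positively assigns the row to one arm. If the full protocol differs, the published table is wrong.

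**Conclusion.** The point holds in a limited form. By its own key, Table 2 schedules adverse event and safety assessment for about 196 of 392 participants, all in the intervention arm. Adverse events that are not also study outcomes cannot be compared between arms. Falls and musculoskeletal injury have no control-arm measure at all; symptomatic hypotension, hypoglycaemic episodes and worsening of an existing ulcer have only partial or indirect ones. Evidence on the most serious harms remains available, and the primary analysis is untouched.

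The conclusion assumes that Table 2 is to be read by its printed note and that no unseen document overrides it. The precision figures rest on assumed risks of 10% to 30% and serve only to show what collection in both arms would yield. Severity: should be fixed.

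**What to change.** First, confirm whether the single X is intended. If it is a slip, correct the row so that the article agrees with the full protocol.

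If it is intended, change X to XX at 12 and 24 months and use one adverse event form, with the same definitions and recall period, in both arms. The remote contacts and record extraction at those times already include the control arm. Tabulate events by randomised arm with risk differences and 95% confidence intervals. Report any log of events during programme sessions separately, for the intervention arm only, and keep it out of the between-arm comparison.

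The cost is a short extra form for about 196 control participants, the associated data handling, and a minor amendment. No new visit is needed, and the sample size and primary analysis do not change.
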